A potential patient who meets any of the following criteria will be excluded from participation in this study:Patients heterozygous or homozygous for the A-allele at rs12608932 (*UNC13A*).Safety Laboratory Criteria at baseline:ALT ≥ 5 times upper limit of normal (ULN)AST ≥ 3 times ULNBilirubin ≥ 1.5 times ULNPlasma sodium <120 mmol/LCreatinine clearance < 50 mL / min (Cockcroft-Gault) based on Cystatin C; if not available, eGFR can also be calculated based on creatinine clearance.Platelet concentration of < 100 × 109 per LAbsolute neutrophil count of < 1 × 109 per LHemoglobin < 100 g/L (<6.2 mmol/L)Amylase and lipase ≥ 2 times ULN (suspected pancreatitis)Lactate ≥ 2 times ULN (suspected lactate acidosis)Moderate to severe hepatic impairment according to Child-Pugh classification (Class B or higher; score ≥ 7). Child-Pugh classification is based on bilirubin, albumin, International Normalized Ratio (INR) and presence of encephalopathy or ascites.Participation in any other investigational drug trial or using investigational drug (within 30 days prior to screening).Hypothyroidism unresponsive to thyroid hormone supplementation.Patients using non-invasive ventilation (NIV, ≥22 h per day) or having a tracheostomy.Patients taking edaravone within 30 days prior to screening. Edaravone is approved by the FDA, but remains an investigational product in Europe and Australia.Clinically significant history of unstable or severe cardiac (e.g., congestive heart failure, coronary insufficiency and arrhythmias), oncological, hepatic or renal disease, neuromuscular diseases, significant pulmonary disorder or other medically significant illness.Drug or alcohol abuse.Bipolar disorder, unstable psychiatric illness defined as psychosis or untreated major depression within 90 days of the screening visit. This exclusion criterion is based on a prior psychiatric diagnosis that is unstable as determined by the patient’s treating psychiatrist.Presence of frontotemporal dementia which prevents informed consent.Known allergy or hypersensitivity to lithium, or its excipients, or to the components of the placebo.Brain injury with posttraumatic epilepsy or neurologic deficit, excluding a concussion in the medical history. Brain infarction is an exclusion criterion, a transient ischemic attack is not.Addison disease.Patients with the following co-medication: antipsychotics, digoxin and calcium antagonists, carbamazepine, methyldopa, verapamil and diltiazem.Brugada syndrome or family history of Brugada syndrome.

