### Intervention description {11a}

Lithium salts such as lithium carbonate or citrate have been used for the treatment of bipolar disorder for decades for its mood stabilizing properties [9–11]. Within this population, lithium carbonate has been used effectively and safely with adequate monitoring. As such, its side-effects, both short- and long term, are well known. Given the fact that multiple trials with lithium carbonate have been performed in ALS, the side-effects of lithium carbonate in the target population of this study are also well known [14, 15, 20].

The study drug will be produced by TioFarma BV and is available as 400 mg capsules of lithium carbonate or matched placebo. Both the study drug and placebo are matched in appearance and packaging, and taken as capsules. Capsules will be taken once daily, starting with one capsule (400 mg daily) initially titrated up to two or three capsules daily over the first four weeks of treatment, depending on blood lithium levels. Blood levels will be measured at baseline, 7 days (12 h +/− 30 min after previous evening dose), and at 14 days (12 h +/−30 min after previous evening dose). The target range for the lithium plasma level will be between ≥0.4 mmol/l and ≤0.8 mmol/l. Further plasma level measurements will be taken at 21 and 28 days to confirm the target range has been achieved. Ongoing lithium level monitoring will be scheduled for week 8 and week 12, and quarterly thereafter for the duration of the study. Dose adjustments can be made by reducing back to 2 capsules daily or to 1 capsule daily as required. It is anticipated that most patients will remain on 2 capsules throughout the duration of the trial. Sham dose adjustments will also be made to patients on placebo to maintain blinding. Unused drug tablets and packaging will be returned during each visit.

Lithium plasma levels will be stored in the centralized online system (Research Online and Castor). Lithium plasma levels are sent to a dedicated mailbox for review by unblinded physicians. They will enter the new dose in the eCRF; subsequently the patient and the site staff will be notified. Study personnel should verify with the patient (by email or phone) that the dose adjustments resulting from the day 7 and day 28 lithium blood draw have been received and understood. On average the lithium levels will be stable after approximately three to four weeks (or 3–4 blood samples).

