Patients will be withdrawn from the study by the Investigator in consultation with the coordinating Investigator and the Sponsor in case of:Liver toxicity where one or more of the following criteria (in alignment with the FDA premarketing clinical liver safety guidance) are met and no compelling alternate cause is):ALT ≥ 3×ULN and bilirubin ≥2×ULN (>35% direct bilirubin)ALT ≥ 5×ULNALT ≥ 3×ULN and with symptoms believed to be related to liver injury or hypersensitivity.ALT ≥ 3× baseline ALT and with symptoms believed to be related to liver injury or hypersensitivity.Allergic reaction criteria are met and no compelling alternate cause is identified:° CTCAE Grade III/IV: severe skin reaction (Steven-Johnson syndrome, Toxic Epidermal Necrolysis or Erythema Multiforme). Patients with Grade ≥3 allergic reactions that are considered to be possibly or probably related to the investigational product should permanently discontinue the investigational product regimen and the patient should be withdrawn from the study. Patients should be treated as clinically appropriate and followed until resolution of the adverse event.° Patients may continue investigational product for CTCAE Grade I or II allergic reactions at the discretion of the Investigator. The patient should be advised to contact the Investigator immediately if there is any worsening of symptoms or if further systemic signs or symptoms develop. Antihistamines, topical corticosteroids, or antipruritic agents may be prescribed.° If a profuse, purpuric and coalescing leukocytoclastic vasculitis occurs, the patient should be withdrawn from the study.Development of moderate to severe renal impairment as measured by Cystatin C (< 50 mL/min).Note: In case of renal impairment, medication may be stopped for 2 weeks, after which the patient is retested. If the renal impairments persist, patients are withdrawn from the study.The patient becomes pregnant.Noncompliance with the protocol as judged by the investigator.

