#### Secondary outcomes

Combined effect on daily functioning and overall survival based on a joint model of survival and ALSFRS-R total scores.Daily functioning, defined as mean change from baseline in ALSFRS-R total score. Disease progression will be monitored using the ALSFRS-R, which is a validated 12-item questionnaire designed to evaluate the functioning of respiratory, bulbar, fine and gross motor function in ALS patients [22]. The total score ranges from 48 (no limitation in daily activities) to 0 (total inability). The ALSFRS-R slope, the difference in scores standardized for time, is often used as measure of disease progression in clinical trials and is significantly associated with survival [23].Respiratory function, defined as mean change from baseline in Slow Vital Capacity (SVC). The SVC is associated with survival in ALS patients [24]. The obtained estimates of the vital capacity will be recorded in liters and standardized using the GLI-2012 reference standard [25].Change in outcome of Plasma creatinine. Plasma creatinine is a part of the safety tests and will be used as one of the secondary endpoints to monitor disease progression [26]. Plasma creatinine is well correlated with functional decline, muscle strength and is highly predictive for overall survival. Due to the effect of disease progression on plasma creatinine, Cystatin C will be used for monitoring kidney function as safety parameter [27].Clinical disease stage, defined as mean time spent in each stage of the King’s and ALS Milano-Torino staging systems. The King’s staging system is a simple clinical staging system, which defines four stages of ALS. The first three stages are defined by functional involvement of a region: bulbar, upper limbs and lower limbs. The number of regions involved gives the stage. Stage 4 is reached if swallowing (4A) or respiratory (4B) difficulty is severe enough to require intervention. This procedure takes the form of a semi-structured interview. MITOS is a similar clinical staging system, in which the stages are defined as loss of independence on the four domains of the ALSFRS-R: swallowing, walking/self-care, communicating and breathing [28]. Studies have shown that both King’s staging and the ALS-MITOS correlate with survival [29, 30].Safety based on the safety assessments including neurological examinations, clinical laboratory evaluations, vital signs and frequency of adverse events (AEs) or serious adverse events (SAEs). (S)AEs will be categorized according to the Common Terminology Criteria for Adverse Events and will be rated for severity and association with study drug.Tolerability defined as time-to-discontinuation of assigned treatment since randomization.Change from baseline in urinary P75^ECD^. P75 is a neutrotrophin receptor that is expressed after motor neural damage and excreted through the urine [31]. Hence, presence of P75^ECD^ in the urine is indicative for the degeneration of motor neurons. P75^ECD^ has been shown to increase over time in patients with ALS and correlates well with measures of functional decline. Moreover, the marker is associated as independent predictor of survival. Therefore, P75^ECD^ may have the utility as a potential pharmacodynamic biomarker and slowing of a rising urine level may be indicative of a biological effect.Change from baseline in plasma Neurofilament light and heavy chain. Neurofilament light and heavy chains in ALS are well known to be correlated with prognosis and remain relatively stable over time [32]. A change in the expression of neurofilament light and/or heavy chain may, therefore, be considered as supporting evidence of disease amelioration in ALS.Neuropsychological status, defined as change from baseline on the ECAS and ALS-FTD-Q. Approximately 35% of the patients, with ALS, experience cognitive or behavioral impairment. The cognitive and behavioral impairment may increase as disease progresses [33]. The neuropsychological status of patients will be evaluated using the Edinburgh Cognitive and Behavioral ALS Screen (ECAS) [34]. The ECAS is independent of motor disability and evaluates five cognitive domains: language functions, executive functions, and letter fluency, memory and visuospatial functioning. If available, ECAS version A and B will be alternated to prevent a training effect in patients. The questionnaire has a behavior screen with a carer interview, this part will not be performed in this study. In addition, we will evaluate behavioral disturbances using the ALS frontotemporal dementia questionnaire (ALS-FTD-Q) [35]. The ALS-FTD-Q is a validated instrument for the screening of behavioral disturbances in ALS. The ALS-FTD-Q has 25 items (including three cognitive items: memory, concentration, and orientation in time), with a 4-point rating scale; the maximum score is 100. A higher score indicates more behavioral disturbances.Global quality of life (QoL), defined as change from baseline on the visual analog scale (single-item scale) and EQ-5D. QoL will be measured using a visual analog scale (single-item scale): a horizontal line of 100 mm ranging from 0 (worst imaginable QoL) to 100 (perfect QoL) [36]. Generic QoL will be measured using the EQ-5D. The EQ-5D measures the health status in terms of five dimensions: mobility, self-care, usual activities, pain and depression. From the EQ-5D a quality-adjust life year (QALY) can be calculated, which is required for cost-utility analysis if a drug is beneficial for patients with ALS [37]. If a patient deceases during the follow-up period, the date will be recorded. If a patient reaches the criteria for respiratory insufficiency (tracheostomy or the use of non-invasive ventilation for ≥22 h per day for ≥10 consecutive days), the date this criterion was met will be recorded and the patient will no longer be part of the study. The time point for all secondary outcomes is month 24.

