#### Analysis populations

*The efficacy population* will be used for the primary efficacy analysis. The efficacy population includes all randomized patients irrespective of follow-up or receiving the actual study medication (intention-to-treat). Patients will be analyzed according to their randomization assignment.*The safety population* will consist of all randomized patients who received at least one dose or portion of a dose of study medication. Patients will be analyzed according to the treatment they received.

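### The renal exclusion attaches a creatinine formula to cystatin C, and its creatinine fallback does not match the cystatin C-only withdrawal limit of 50 mL/min

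*Protocol article*

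**What the plan says.** Eligibility criteria {10} lists, among the baseline safety laboratory exclusions, a creatinine clearance below 50 mL/min. The formula and marker follow in the same line: "Cockcroft-Gault) based on Cystatin C; if not available, eGFR can also be calculated based on creatinine clearance".

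The withdrawal criteria (Criteria for discontinuing or modifying allocated interventions {11b}) use the same number with one marker and no alternative: "Development of moderate to severe renal impairment as measured by Cystatin C (< 50 mL/min". A note adds "In case of renal impairment, medication may be stopped for 2 weeks, after which the patient is retested", and then "If the renal impairments persist, patients are withdrawn from the study".

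The reason for preferring cystatin C is under Secondary outcomes, where plasma creatinine is an endpoint: "Plasma creatinine is well correlated with functional decline, muscle strength and is highly predictive for overall survival". The article continues: "Due to the effect of disease progression on plasma creatinine, Cystatin C will be used for monitoring kidney function as safety parameter".

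**The concern.** There are two separate problems.

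The first is the wording of the main limb. It names a creatinine formula and says that the formula is based on cystatin C. A site can follow the marker and report a cystatin C eGFR, or follow the formula and calculate a creatinine clearance even where cystatin C is on hand. Safety assessments are evaluated locally (Plans for assessment and collection of outcomes {18a}) at centers in six countries (Study setting {9}), so different sites could apply different rules.

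The second is the fallback. It admits patients on a marker that the article regards as disturbed by the disease, while withdrawal is judged at the same cut-off on the other marker. If creatinine is low because muscle has been lost, clearance is overestimated. A patient could then start lithium below the limit that the trial sets for stopping it, and later be withdrawn although kidney function has not changed.

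**Working it through.** The 50 mL/min is a chosen cut-off, so there is no derived figure to reproduce. The check compares the texts and then illustrates the possible size.

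**1. Can the main limb be calculated?** Cockcroft-Gault is (140 − age) × weight / (72 × serum creatinine), times 0.85 for women. Its inputs are age, weight, sex and serum creatinine. A cystatin C value has nowhere to go, so the main limb has no literal value. The fallback can be calculated.

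**2. Do entry and withdrawal match?**

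| | Limit | Marker | Alternative |
|---|---|---|---|
| Exclusion {10} | 50 mL/min | cystatin C, labelled Cockcroft-Gault | creatinine |
| Withdrawal {11b} | 50 mL/min | cystatin C | none |

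They match for a patient tested on cystatin C at entry, once the label is corrected. They do not match for a patient admitted on the fallback. The sentence under Secondary outcomes is about monitoring, but every participant already has ALS at entry, so its reasoning applies at baseline too.

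**3. Does the pause and retest resolve the mismatch?** No. If kidney function has not changed, a second cystatin C result two weeks later is still below 50.

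**4. When would it come to light?** In Table 1 the full blood sample is taken at baseline and next at month 3. Between them, at days 7, 14, 21, 28 and 56, only lithium-level draws are listed. Titration occupies the first four weeks (Intervention description {11a}), so a fallback patient can complete it with no scheduled cystatin C result.

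**5. How large could the gap be?** The article gives no creatinine or cystatin C values, so everything in this step is assumed: a creatinine reduction r of 10%, 20% or 30%; a weight ratio w of 1 (stable) or 0.9 (10% loss); Cockcroft-Gault as the fallback; and cystatin C reading the true clearance. The formula is proportional to weight and inversely proportional to creatinine, so

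- fallback reading = true clearance × w / (1 − r)
- highest fallback reading with cystatin C below 50 = 50 × w / (1 − r)
- lowest true clearance that still reads 50 = 50 × (1 − r) / w

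| r | w | Highest reading with cystatin C below 50 | Lowest true clearance that reads 50 | True clearances wrongly admitted |
|---|---|---|---|---|
| 10% | 1 | 50/0.9 = 55.6 | 50 × 0.9 = 45 | 45–50 |
| 20% | 1 | 50/0.8 = 62.5 | 50 × 0.8 = 40 | 40–50 |
| 30% | 1 | 50/0.7 = 71.4 | 50 × 0.7 = 35 | 35–50 |
| 10% | 0.9 | 45/0.9 = 50.0 | 45/0.9 = 50.0 | none |
| 20% | 0.9 | 45/0.8 = 56.3 | 40/0.9 = 44.4 | 44.4–50 |
| 30% | 0.9 | 45/0.7 = 64.3 | 35/0.9 = 38.9 | 38.9–50 |

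In all six cases more marked impairment is still excluded. Weight loss works against the bias, because it lowers the Cockcroft-Gault reading.

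**The case against.** The strongest reply is that this is a misplaced label plus a rare edge case. The intended order is readable: cystatin C first, creatinine if it is unavailable, limit 50 mL/min. Choosing a cystatin C equation is a detail that an article may leave to the full protocol. This stands in part. The missing equation is not a fault here, and a reader should not infer that the criterion is unworkable in practice. But the article states a wrong pairing of formula and marker in a safety threshold for lithium, and condensation does not explain that. Correcting the label would also leave the fallback mismatch in place.

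A second reply is that the withdrawal rule speaks of impairment that develops, so a patient whose kidneys have not changed need not be withdrawn. This also stands. It is tempting to say that the two rules contradict each other and that fallback patients will be withdrawn for no reason, but the wording does not go that far. On the narrow reading, however, a patient below the trial's own renal limit stays on lithium. On the broad reading the patient is withdrawn without any renal change. Neither outcome is wanted.

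Third, the affected group may be very small: cystatin C must be unavailable at baseline, available later, and true clearance must lie somewhat below 50. Sites need the assay for on-treatment monitoring anyway. Nothing in the article contradicts this, and it limits the weight of the point.

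Fourth, exposure is controlled directly. Treatment starts at 400 mg daily, and lithium is measured at days 7, 14, 21 and 28. After that, "Ongoing lithium level monitoring will be scheduled for week 8 and week 12, and quarterly thereafter for the duration of the study". The side-effect questionnaire, the discontinuation limits and the exclusion of significant renal disease add protection. These do limit harm. They detect exposure or symptoms, however, and do not apply the renal limit.

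**Conclusion.** The point holds in limited form. The main limb of the renal exclusion is mis-worded and cannot be calculated literally. The fallback lets in patients on a marker that the article distrusts, at a cut-off that is later enforced on another marker.

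Neither the frequency nor the size of the problem can be derived from the article. Under the assumptions above, the true clearances wrongly admitted run from none (10% reduction with 10% weight loss) to 35–50 mL/min (30% reduction at stable weight). These figures illustrate a range and are not estimates.

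A reader might infer a threat to the efficacy result. The article does not support that: no event count, power or alpha figure depends on this criterion, and "The efficacy population includes all randomized patients irrespective of follow-up or receiving the actual study medication (intention-to-treat". This is a matter of eligibility and safety wording that deserves correction at the next amendment, mainly because the drug is lithium and the change is cheap.

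**What to change.** - In Eligibility criteria {10}, state the exclusion as cystatin C-based eGFR below 50 mL/min, with the same equation and units as the withdrawal rule in {11b}. Attach Cockcroft-Gault only to the creatinine fallback.
- Obtain the cystatin C result before randomization, within the 45-day screening window in Table 1, wherever possible. A test first done after randomization would turn a screening failure into an early stop.
- Only where that is impossible, allow the fallback, and require cystatin C on the first available sample, for example the day 7 lithium draw, with the 50 mL/min limit applied to it.

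The cost is amendment wording and some sample handling. Table 1 lists no safety blood sample at screening, so a result before randomization needs either a tube at that visit or a baseline result in hand before allocation. Since about 1200 patients are screened for 171 places, a screening tube should be assayed only in those with the qualifying genotype. Some sites will have to send a sample to another laboratory, and a few patients will be excluded, or stopped earlier, than under the current text. The fallback test shares a scheduled draw and adds no visit.

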
### Who will take informed consent? {26a}

Prior to performing any study-related activities under this protocol, including screening tests and assessments, written informed consent (IC) will be obtained from the patient. The patient information will be provided prior to the screening visit. A trial physician will conduct the IC process and inform patients on the details of the study. The trial physician will sign the informed consent after the patient indicates that he or she has been given enough time to consider participation, and when all questions are adequately answered. A copy of the IC, signed and dated by the patient and trial physician, is given to the patient. Confirmation of a patient’s IC will be documented in the patient’s medical record.

### Additional consent provisions for collection and use of participant data and biological specimens {26b}

An option for permission to reuse clinical data and any blood and urine not fully used in the current study is included in the IC form. If patients have given consent to perform a lumbar puncture, the same applies to any remaining cerebrospinal fluid.

## Interventions

### Explanation for the choice of comparators {6b}

A matched placebo will be used. The use of a placebo group provides us the ability to distinguish between effects directly caused by the active drug and those effects resulting from variation in disease progression. Optimal standard of care will be offered to all patients in addition to study medication. Changes in care after randomization (e.g., stop of Riluzole, gastrostomy placement, or use of non-invasive ventilation) are permissible and will be registered as potential intercurrent events.

